**Fig. 2 Fig2:**
[figure not shown]
Visit plan. DIPS, Diagnostic Interview for Psychological Disorders [61]; Mini-DIPS, short form of the Diagnostic Interview for Psychological Disorders [62]; CTS, Childhood Trauma Screener [63]; EXIS.pers, Experience in Personal Social Systems Questionnaire [64]; TAI, Therapeutic Agency, therapeutic-processing subscale [65]; NEQ, Negative Effects Questionnaire – 20 Item Version [66]; NoMAD, Normalization Measure Development questionnaire [67]; GEEE, Generic rating scale for previous treatment experiences, treatment expectations, and treatment effects [68]; W&C, Warmth and Competence Scale [69]; SOMS-7R, Screening for Somatoform Disorders – revision [70, 71]; WAI-SR, Working Alliance Inventory [72]; SSD-12, Somatic Symptom Disorder – B Criteria Scale [73]; PHQ-9, Patient Health Questionnaire – depression scale [74]; FESV, Pain Coping Questionnaire – coping subscales [75]; GAD-7, Generalized Anxiety Disorder Questionnaire [76]; WI, Whiteley Index [77]; WHOQOL-BREF, World Health Organization Quality of Life questionnaire [78]; PDI, Pain Disability Index [44]; FESS, Pain Self-Efficacy Questionnaire [79]; HCU-Q, Health Care Utilization Questionnaire [80]; ZUF-8, Client Satisfaction Questionnaire [81]; ^a^filled out by therapists; ^b^only in intervention condition; ^c^this external examination should be conducted up to visit 2 and visit 3 at the latest; ^d^assessed as part of the pre-screening; ^e^In both study arms, adherence and intervention usage will be continuously assessed throughout the treatment

### Provisions for post-trial care {30}

There is no ancillary post-trial care or compensation specifically related to study participation beyond routine care. Participants are covered by participant insurance and travel insurance for any study-related harms. Participants receive guideline-approved outpatient psychotherapy within the German statutory health care system throughout the study period. If clinically significant psychological distress or ongoing treatment needs remain after completion of the intervention (session 20), continued treatment within routine care will be recommended. Depending on individual clinical needs, participants may continue psychotherapy or be referred to access additional appropriate psychotherapeutic, psychiatric, psychosocial, or counselling services. Decisions regarding further care will be made by the treating psychotherapist and supervisor in accordance with clinical needs and standard practice.

### Outcomes {12}

The selection of outcome measures was based on the guidelines for clinical trials in patients with PSS by the European Research Network to Improve Diagnosis, Treatment and Health Care for Patients with Persistent Somatic Symptoms (EURONET-SOMA) [82]. Of main interest is the absolute change in scores in patient reported questionnaires from baseline (t0) to end of treatment (t1), the latter constituting the primary endpoint. The *primary outcome* will be self-reported somatic symptom severity, assessed using the revised version of the Screening for Somatoform Disorders (SOMS-7R [70, 71]) at baseline, during treatment (face-to-face sessions 1, 5, 10, and 15), post-treatment, and up to 6-month follow-up. Somatic symptom severity represents one of the core outcome domains in both research and clinical practice and is of high relevance to patients. It is considered as a continuous score and of primary interest is the absolute change from baseline (t0) to end of treatment (t1). The treatment differences will be displayed by a linear contrast for each study visit from the model with their 95% confidence intervals. The primary analysis population is the intention-to-treat (ITT) population consisting of all patients randomized. Long-term maintenance of the primary outcome, somatic symptom severity, will be evaluated using SOMS-7R scores at the 6-month follow-up. Additionally, we will qualify response and remission by change scores of the primary outcome (SOMS-7R) and remission by change in diagnostic status from baseline up to follow-up as categorical change parameters.

*Secondary outcomes* will be assessed at baseline, post-treatment and at the 6-month follow-up and will include the following constructs and questionnaires: adverse psychobehavioral consequences of somatic symptoms (Somatic Symptom Disorder – B Criteria Scale, SSD-12 [73]), symptom coping (Pain Coping Questionnaire, FESV, coping subscales [75]), health related self-efficacy (Pain Self-Efficacy Questionnaire, FESS [79]), depression (Patient Health Questionnaire – depression scale, PHQ-9 [74]), anxiety (Generalized Anxiety Disorder, GAD-7 [76]), health anxiety (Whiteley Index, WI [77]), disability (Pain Disability Index, PDI [44]), quality of life (World Health Organization Quality of Life questionnaire, WHOQOL-BREF [78]), and experience in personal social systems (Experience in Personal Social Systems Questionnaire, EXIS.pers [64]). *Mediators* of treatment effects will include self-efficacy (assessed via FESS), treatment agency (assessed via the therapy-oriented processing subscale of the Therapeutic Agency Inventory, TAI [39, 65]), and disability (assessed via PDI). Mediators will be assessed at baseline, during treatment (sessions 1, 5, 10, 15), post-treatment, and at follow-up. *Potential moderators* of the treatment-related change processes will be explored. These will be assessed at baseline and will include (a) demographic variables, (b) clinical characteristics (e.g., comorbidity, baseline symptom severity, traumatic experience via the Childhood Trauma Screener (CTS [63])), and (c) treatment characteristics (e.g., parallel treatments, type of referral, preferences, treatment expectations assessed via the Generic rating scale for previous treatment experiences, treatment expectations, and treatment effects (GEEE [68])). Health care utilization (Health care Utilization Questionnaire, HCU [80]) will be assessed at baseline, post-treatment and at follow-up. In addition, therapist behavior and therapeutic alliance will be assessed during treatment (sessions 1, 5, 10, and 15) using the Warmth & Competence Scale (W&C [69]) and the Working-Alliance Inventory – short revised (WAI-SR [72]). General treatment satisfaction will be assessed post-treatment using the Client Satisfaction Questionnaire (ZUF-8 [81]), and module-specific satisfaction and perceived effectiveness of iSOMA will be assessed using self-constructed items. The extent to which iSOMA is a normal part of the daily working routine of therapists will be assessed post-treatment with the Normalization Measure Development questionnaire (NoMAD [67]). In both study conditions, adherence and duration of intervention use will be continuously monitored throughout the treatment period using self-constructed items. Self-rated negative treatment effects will be assessed post-treatment by the Negative Effects Questionnaire (NEQ [66]). Psychotherapists will provide sociodemographic data and indicate treatment preference at baseline and monitor SAEs and events of special interest (ESIs) and protocol deviations throughout treatment (sessions 1, 5, 10 and 15), post-treatment and at follow-up (administered by study personnel).

### Participant timeline {13}

Individuals expressing interest will be subjected to a telephone (or in-person) interview to determine preliminary inclusion and exclusion criteria (pre-screening), accompanied by filling out questionnaires for screening purpose (basic patient data, PHQ-15, PDI). Preliminary eligible individuals will then be invited to a personal informational interview. During the course of the interview, the participants will be provided with comprehensive information and written consent will be obtained. The diagnosis of SSD will be confirmed based on the Diagnostic Interview for Psychological Disorders (DIPS; [61]), which will be administered by independent, experienced therapists. If eligibility criteria are met and the patient agrees to participate by signing the informed consent, they will be asked to complete the baseline survey (t0). Afterwards, participants will be assigned to their study therapist and the regular, health insurance-covered therapy regimen will continue, starting with up to four probatory sessions. In the initial two probatory sessions, which are mandatory preliminary appointments in the German health care system to assess diagnosis, treatment indication, and therapeutic fit, the study therapists will continue the diagnostic process using the short form of the diagnostic interview (Mini-DIPS; [62]) to assess potential exclusion criteria (SSD not main diagnosis) or further comorbid diagnoses. Patients will be referred for routine care medical check-up (“Konsiliarbericht”) to identify medical red flags that prevent safe trial participation. In cases of uncertainty, a medical supervisor will be available for consultation regarding the clarification of potential red flags. If all inclusion criteria are fulfilled, participants will be randomly assigned to one of the two study arms automatically within the electronic database (randomization, allocation). In the third probatory session, participants in the intervention group will be granted access to iSOMA, while those in the control group will be provided with the self-help booklet. Patients will then receive 20 sessions of blended psychotherapy or enhanced psychotherapy, respectively, in accordance with the session protocol depicted in Table 1. At therapy sessions 1, 5, 10, and 15, the primary outcome and putative mediators will be assessed (paper-based or digitally). In addition, the therapists will document changes in concomitant treatments (e.g., medical treatments), SAEs/ESIs that could influence the study therapy, and actions taken (e.g., after consultation with supervisor and/or study head). At the end of treatment (after 20 sessions, regular end of therapy or discontinuation of therapy), participants will complete the post-treatment assessment (paper-based or digitally). Therapists in the blended psychotherapy condition will also complete a brief questionnaire assessing their experience with the implementation of the online platform into treatment. Patients will be invited to a diagnostic telephone interview administered by the study personnel. Six months after the end of treatment, patients will complete a follow-up survey (paper-based or digitally) and will also be invited to another diagnostic interview via telephone. Figure 2 presents the participant timeline and the scheduling of the assessments.

### Sample size {14}

Short-term CBT has demonstrated predominantly small to medium-sized between-group effects on somatic symptom severity in patients with medically unexplained physical symptoms or somatoform disorders (Standardized Mean Difference; *SMD* = 0.37; [18]) and medium- to large-sized within-group effects (*SMD* = 0.80; [83]), as corroborated by a multicenter CBT trial in outpatients with PSS (Cohen’s *d* = 0.70; [51]). Stand-alone internet-delivered CBT yielded small-sized average between-group effects on this outcome (*SMD* = 0.35; [84]) across chronic pain and functional somatic syndromes, whereas evidence from RCTs in individuals with diagnosed/probable SSD demonstrated medium- to large-sized effects (*d* = 0.68 to 0.91) [57, 85]. Evidence from depression research indicates small to medium-sized effects (*d* = 0.32 to 0.51) [34, 86] of added internet interventions to outpatient psychotherapy, which mirrors the treatment setting in the current study. Taken together, we expect the difference between our blended treatment and the enhanced treatment to be *d* = 0.40 for the primary endpoint. Thus, with a power of 80%, and a significance level of 0.05 (two-sided), 200 patients are required, when using a t-test. Because of some variability in effect sizes in the literature and the multicenter study introducing additional heterogeneity we planned the sample size conservatively by not using any correlation between measurements or between outcome and baseline variables. Based on treatment studies in this research field we expect a study drop-out for our primary endpoint (t1) up to 20% [51, 87], resulting in a sample size of *N* = 250 (125 per group). A study in the same setting concluded a similar sample size of 194 [51]. The calculation was performed with SAS 9.4.

### Recruitment {15}

The study centers recruit patients through self-initiated inquiries from individuals seeking psychotherapy in general and through targeted inquiries specifically for the study. To reach potential participants, informational materials (e.g., flyers, posters) are distributed in local medical treatment centers such as medical practices and clinics (e.g., psychosomatic-, pain-, or rehabilitation clinics). The study is also promoted through newspapers, newsletters, and social media. Furthermore, self-help groups are contacted and encouraged to share the informational materials with their members.

## Assignment of interventions: allocation

### Sequence generation {16a}

A randomization list is generated at Interdisciplinary Center for Clinical Trials (IZKS) at the University Medical Center Mainz by means of a validated SAS program (9.4 (SAS Institute, Cary, NC, USA)). The randomization ratio of the treatment group and the control group will be 1:1. Randomization will be stratified by study center. Block randomization with different block size will be applied.

### Concealment mechanism {16b}

Allocation concealment will be ensured through the eCRF-based randomization system. Treatment assignment will be generated automatically only after eligibility has been confirmed and participant enrollment has been completed. The randomization list will be kept in safe and confidential custody at IZKS Mainz and is not accessible to investigators, therapists, assessors, and other site personnel.

### Implementation {16c}

The randomization list will be generated by an otherwise study independent person at the IZKS. Treatment assignment will be performed automatically by the central eCRF-based randomization system. Eligible participants will be enrolled by qualified study personnel at the study sites.

## Assignment of interventions: blinding

### Who will be blinded {17a}

Blinding of patients and therapists is not possible due to the nature of the treatment. The raters (scoring personnel who evaluate the outcome questionnaires) and data analysts will be blinded to treatment allocation. Diagnostic assessments will be conducted by assessors who are independent of treatment delivery but are not formally blinded to treatment allocation. Data analysts will remain blinded until the database has been completed and locked.

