
### Objectives {7}

The primary objective of this trial is to investigate the efficacy, that is to show that an integrated form of blended psychotherapy (iSOMA+) reduces somatic symptom severity significantly stronger than CBT enhanced with bibliotherapy (CBT+) from baseline to post-treatment.

Furthermore, we expect that iSOMA+, compared to CBT+, will lead to significantly greater reductions in secondary outcomes, including somatic symptom severity, adverse consequences of somatic symptoms, depression, anxiety, health anxiety and disability as well as significantly greater improvements in self-efficacy, somatic symptom coping, quality of life and experience in personal social systems from baseline to post-treatment and from baseline to the 6-month follow-up.

Thirdly, we expect that iSOMA+, compared to CBT+, will lead to a significantly higher rate of meaningful clinical change (response, remission) in somatic symptom severity.

Fourthly, we will investigate mechanisms of action, since previous trials have identified that motivational (e.g., self-efficacy, treatment agency) and functional (e.g., pain-related disability) characteristics are positively associated with treatment outcomes and may act as mediators of therapeutic change [39–41]. However, their role in blended psychotherapy is unclear. Therefore, we test whether an increase in self-efficacy, treatment agency, and a reduction in functional impairment will mediate the treatment effect of iSOMA+ compared with CBT+.

Exploratively, we will investigate to what extent (a) demographic characteristics of patients (e.g., gender), (b) clinical characteristics (e.g., baseline severity of somatic symptom distress, comorbidity), and (c) treatment-related factors (e.g., concurrent treatments, treatment expectations) moderate the treatment effect between the two treatment conditions (iSOMA+ vs. CBT+).

Furthermore, we will examine whether iSOMA+ differs from CBT+ with respect to changes in health care utilization from baseline to the end of treatment and from baseline to the 6-month follow-up. Treatment satisfaction and implementability will be tested. Finally, patient safety will be investigated, and no significant differences are expected in the type or frequency of serious adverse events (SAEs) and other side-effects between iSOMA+ and CBT+.

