## Statistical methods

### Statistical methods for primary and secondary outcomes {20a}

The *primary endpoint* will be analyzed with a linear mixed-effect model (LMM) including center, use of prescribed psychopharmaceutic (ATC code N06A, yes/no), use of other (non-psychopharmaceutic) medications such as analgesics or antihypertensives (yes/no), mental disorder comorbidity (yes/no), intervention, time point, and the interaction term of intervention and time point as fixed effects, as well as baseline value as a covariate. An autoregressive covariance structure will be used as the primary covariance structure, given the ordered repeated measurements and the expected decrease in correlations over time. Robustness will be assessed using alternative covariance structures. The mixed-effects model uses all available observations and provides valid inference under the missing-at-random assumption. Model assumptions will be checked by residual plots and sensitivity to handling of missing data using multiple imputation. The test used is a linear contrast between the groups at post-treatment (time as categorical variable) and uses a *t*-statistic. Treatment differences will be displayed by adjusted mean differences and 95% confidence intervals. Follow-up data will be analyzed by the LMM approach taking a different contrast. The primary analysis will be performed with the ITT-population. For sensitivity additional subpopulations will be analyzed. Descriptive statistics will also be provided over time by treatment and in total. The primary parameter will also be displayed over time by a boxplot. For sensitivity also response and remission in the SOMS-7R are analyzed. Response will be operationalized as percentage improvement relative to the respective baseline score, (≥ 50% improvement within the pathological range of the SOMS-7R + 25% within the full range [93]). Remission will be coded if patients fulfill response criteria and transition from a dysfunctional to a functional score range in the SOMS-7R. As another remission criterion, we will analyze group differences in diagnostic status (SSD criteria fulfilled) at post-treatment and follow-up. Response and remission will be analyzed within a logistic regression model for each time point with the same covariates as the primary model. Descriptive statistics (absolute and relative frequencies) by time point will also be provided. Continuous secondary outcomes will be analyzed within an analysis model analogous to the primary analysis model and descriptive statistics will be given. Variables expected to have a skewed distribution like working disability days will be analyzed by Wilcoxon Rank Sum test. Categorical outcomes will be analyzed by Χ^2^-tests and will also be displayed by absolute and relative frequencies. Exploratively, health care utilization will be analyzed descriptively at the item level and compared between treatment groups. We will descriptively analyze the extent to which iSOMA is a normal part of the daily working routine of therapists’ post-treatment with the NoMAD. We will test group differences in the type and frequency of self-reported side effects in the NEQ with Χ^2^-tests and independent *t*-test for severity ratings. Potential moderators of the change processes between treatments include (a) demographics, (b) clinical characteristics (e.g., comorbidity, baseline symptom severity, traumatic experience via the CTS), as well as (c) treatment characteristics (e.g., parallel treatments, type of referral, preferences, treatment expectations via GEEE) at baseline. Mediators will be assessed at baseline, during treatment (sessions 1, 5, 10, 15), post-treatment, follow-up. We will examine the temporal, contemporaneous, and between-subject interaction of the therapists’ warmth and competence, treatment expectations, alliance, and psychotherapy outcomes with network models. To test the mechanisms of action of the blended therapy, mediating variables (self-efficacy, disability, and treatment agency) will be analyzed with structural equation modelling (SEM), assuming a lagged effect of a respective mediator on the primary outcome (dual simplex model [94]). This way, indirect effects via different pathways leading to the outcome can be examined. Model fit will be evaluated. Exploratory analyzes will examine further effect-modulating variables (e.g., treatment preferences, patient-, clinical, or treatment characteristics) as moderators (i.e., interaction effects with treatment group) or in the form of subpopulation/sensitivity analyzes (e.g., comorbidity status, treatment length, health care utilization) using the same LMMs as for the main analysis.

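### SSD diagnostic remission, the only interviewer-rated efficacy outcome, is assessed by interviewers whose masking is not ensured, so rater bias can affect this additional remission criterion

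*Protocol article*

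**What the plan says.** All quotes are from the protocol article.

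- **Who is blinded.** Under Who will be blinded {17a}: "Blinding of patients and therapists is not possible due to the nature of the treatment". Then: "The raters (scoring personnel who evaluate the outcome questionnaires) and data analysts will be blinded to treatment allocation". For the diagnostic interviews: "Diagnostic assessments will be conducted by assessors who are independent of treatment delivery but are not formally blinded to treatment allocation".
- **Who interviews, and when.** Participant timeline {13} says of the end of treatment: "Patients will be invited to a diagnostic telephone interview administered by the study personnel". At 6 months, patients "will also be invited to another diagnostic interview via telephone".
- **How the interviews are used.** Outcomes {12} plans to report "remission by change in diagnostic status from baseline up to follow-up as categorical change parameters". Statistical methods {20a} adds: "As another remission criterion, we will analyze group differences in diagnostic status (SSD criteria fulfilled) at post-treatment and follow-up". Response and remission are to be analysed by logistic regression at each time point, with the covariates of the primary model.
- **The other efficacy outcomes.** The primary outcome (SOMS-7R) and the listed continuous secondary outcomes are patient questionnaires scored as sums, means or transformed domain scores. SOMS-7R response and remission are calculated from the same self-report.

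**The concern.** Masking is placed where little judgement is exercised and left out where judgement is exercised. A questionnaire total comes out much the same whoever adds it up. Whether a patient still meets SSD criteria depends on an interviewer deciding if the patient's thoughts, feelings and behaviours about symptoms are excessive. An interviewer who knows the arm, in a trial that expects iSOMA+ to be superior, may resolve borderline cases in one direction.

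At stake is the credibility of one prespecified between-arm efficacy comparison at two time points. It is the only efficacy outcome on which masking a rater could add real protection. The assessors are already independent of treatment, so the exposure is largely avoidable.

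**Working it through.** **1. Is diagnostic status the only interviewer-rated efficacy outcome?** Going through Outcomes {12} and Plans for assessment and collection of outcomes {18a}, the SOMS-7R, SSD-12, FESV, FESS, PHQ-9, GAD-7, WI, PDI, WHOQOL-BREF and EXIS.pers are all patient-completed. Treatment-integrity ratings and the SAE/ESI checklists involve a rater but are not efficacy outcomes. Only diagnostic status remains.

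**2. Does another section supply the masking?** Concealment mechanism {16b} keeps the randomization list from assessors. That protects the next allocation. It does not hide a patient's arm at an interview months later. There is also a plausible route to the arm: study staff enter all survey data into the eCRF, and some items exist only in the intervention condition (Fig. 2 legend; iSOMA satisfaction items in Outcomes {12}). The article describes no instruction to patients, no masked second rating and no record of unmasking.

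**3. The number per arm.** The plan's own figures reproduce. For d = 0.40, 80% power and two-sided 0.05, the t-test needs 99.08 per arm, rounded up to 100, so 200 in total; 200 / (1 - 0.20) = 250. The concern challenges neither figure. I borrow 100 evaluable per arm from them; attendance at the interviews is not stated.

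**4. Size, on assumed values.** Let p be the true remission rate in both arms and e the share of iSOMA+ non-remitters rated as remitted, with no such error in CBT+. The protocol gives neither.

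- Observed iSOMA+ rate: p1 = p + e(1 - p). Spurious difference: d = e(1 - p).
- With m = (p + p1)/2: se0 = sqrt(2m(1 - m)/100) and se1 = sqrt([p(1 - p) + p1(1 - p1)]/100).
- False-positive rate = Φ((d - 1.96·se0)/se1) + Φ((-d - 1.96·se0)/se1).

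Example, p = 0.30 and e = 0.10: p1 = 0.37, d = 0.07, m = 0.335, se0 = 0.0668, se1 = 0.0666. The upper tail is Φ(-0.91) = 0.180 and the lower tail Φ(-3.02) = 0.001, together about 0.182.

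| True remission, both arms | e | Observed iSOMA+ rate | Spurious difference (points) | False-positive rate |
|---|---|---|---|---|
| 20% | 5% | 24% | 4.0 | 10.5% |
| 20% | 10% | 28% | 8.0 | 26.2% |
| 30% | 5% | 33.5% | 3.5 | 8.3% |
| 30% | 10% | 37% | 7.0 | 18.2% |
| 40% | 5% | 43% | 3.0 | 7.1% |
| 40% | 10% | 46% | 6.0 | 13.7% |

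A simulation of the same settings (40,000 draws) gave 7.5% to 26.3%. With no misrating the rate is the nominal 5%. These are unadjusted two-group comparisons; the planned logistic regression adjusts for covariates, so the figures show scale only.

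**The case against.** The strongest case on the other side has five parts.

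- **The choice is disclosed and secondary.** This stands. There is no contradiction in the protocol, and diagnostic status is one of two remission criteria.
- **Not formally blinded does not mean that interviewers know the arm.** This stands. A reader might infer that every interviewer is unmasked; the text shows only that masking is not ensured.
- **Masking would not make the outcome independent of the patient.** This stands. A reader might infer that a masked interview is free of the unblinded patient's own rating. It is not: the interviewer works from the account of a patient who knows the arm. Masking removes rater bias and leaves reporting bias.
- **The superiority hypothesis is not about diagnosis.** A reader might link the concern to Objectives {7}, which expects that iSOMA+ "will lead to a significantly higher rate of meaningful clinical change (response, remission) in somatic symptom severity". Somatic symptom severity is the SOMS-7R construct, and Objectives {7} does not name diagnostic status. The documents therefore do not show that rater bias reaches that hypothesis.
- **The misrating is assumed and wholly one-sided.** This stands. Both arms receive the same 20 CBT sessions with content-matched add-ons, so the interviewer's contrast is app against booklet. Nothing in the documents shows error of 5-10% in one arm only.

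It would also be too strong to say that blinding the scorers is worthless. Staff enter paper forms into the eCRF, and blinding has some small value there.

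What remains is that a judgement-based between-arm efficacy outcome lacks a protection that staff already independent of treatment could largely provide.

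**Conclusion.** The concern holds as a design weakness that should be corrected. The protocol leaves unensured the masking of the one efficacy outcome that an interviewer rates, and compares it between arms at post-treatment and follow-up. Rater bias can therefore affect the additional, diagnosis-based remission criterion. It does not touch the primary endpoint, the sample size or the SOMS-7R response and remission outcomes.

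The illustrated size, 3-8 points and a false-positive rate of about 7-26%, rests entirely on four assumptions: equal true remission of 20-40%, 100 interviewed per arm, 5-10% misrating in iSOMA+, and none in CBT+. It shows that modest one-sided error would matter. It is not evidence that such error will occur.

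**What to change.** Change Who will be blinded {17a} so that the post-treatment and follow-up diagnostic interviewers are masked, using existing staff:

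- Hide allocation and add-on fields (iSOMA usage, booklet use, arm-specific items) from the interviewers' eCRF role.
- Assign interviewers who did not handle that patient's allocation or arm-specific data, for example by exchanging interviews across centres.
- Open each interview with a short standard request that the patient not mention the add-on.
- Record in the eCRF whether unmasking occurred and which arm the interviewer guesses.

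Report unmasking by arm. Do not rely on an analysis that drops unmasked interviews: unmasking happens after randomization, and if app users mention their add-on more often than booklet users, the exclusion would itself introduce selection bias. Where masking is not achieved, including any interviews held before the change, label diagnostic remission as open-label assessed.

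The cost is an eCRF role setting, a short opening text and two eCRF items, plus some rearrangement of roles. That last part may not be trivial at eight sites, because study personnel also administer the SAE/ESI assessment at these two time points and study staff enter the survey data. The article gives no staffing numbers. Some patients will still reveal their arm.
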